## Study protocol

### Study objectives

1.Establish the safety of experimental pneumococcal inoculation in PLHIV and the acceptability of the procedure to participants.2.Establish the rate and density of pneumococcal carriage in PLHIV compared to HIV negative adults after experimental pneumococcal inoculation.3.Identify the immune correlates of protection from pneumococcal carriage in PLHIV following experimental pneumococcal inoculation.

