### Study hypotheses

PLHIV will exhibit higher carriage rate and density than HIV-negative controls following experimental pneumococcal inoculation.PLHIV will have perturbed mucosal and systemic immunity in response to experimental pneumococcal inoculation, compared to HIV-negative controls, which will predispose them to pneumococcal carriage.

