### Determination of colonisation

Pneumococcal colonisation will be assessed by conventional microbiological culture from nasal washes obtained from participants, and also confirmed by molecular methods (lytA polymerase-chain reaction-based methods). Pneumococcal colonisation is defined as the detection of pneumococcus serotype 6B by microbiological culture in nasal wash samples at any of the time points on days 2, 7, 14 and 21 post-inoculation, as previously described
^
19
^. The density of colonisation will be measured by classical microbiological culture and molecular methods.

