### Sampling methods

Sampling methods used in this study have been successfully used during the PCV13 study at MLW, and are well-tolerated by participants
^
2,
20
^.

**
*Nasosorption:*
** An absorptive strip is held inside the nose for 3 minutes to collect concentrated nasal lining fluid.

**
*Nasal wash:*
** Five millilitres of sterile saline solution are instilled per naris with the participant in a semi-recumbent position. Participants are instructed to close their soft palate and hold the saline in the nares for a few seconds before leaning forward to allow the fluid to drip into a sterile Galli pot.

**
*Nasal curettage:*
** The cup-shaped end of a plastic, single-use rhinoprobe is grazed along the lower nasal turbinate of each nostril to collect nasal cells.

**
*Throat swab:*
** Simple posterior pharyngeal swabbing on a dry swab for viral co-infection testing.

**
*Venepuncture:*
** Venepuncture will be performed to ensure participants are fit to participate, to evaluate peri-inoculation serum levels of commonly used antibiotics, and to evaluate peripheral blood immune dynamics.

**
*Saliva:*
** salivette held for saturation or a spit in the tube.

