### Safety monitoring

This will be the first CHIM study in PLHIV and participant safety is paramount. Experimental pneumococcal carriage is expected to be a benign event due to the pervasiveness of natural pneumococcal carriage in PLHIV and the low carriage to disease ratio. In the unlikely event that invasive pneumococcal disease develops in a study participant, robust safety monitoring will identify signs of invasive disease early and enable immediate treatment. Participants will be housed in study accommodation for the first three days following inoculation, as invasive disease tends to occurs early during carriage acquisition. Participants will have a symptoms-review and vital-signs check at every study visit. Any abnormalities will trigger a formal clinical review by a study doctor. In between study visits, participants will have phone contact with the study team to establish that they are well and apyrexial. An escalation protocol is established if participants are not contactable. An on-call doctor is available for participants 24/7 and participants are given written and verbal instruction on when and how to contact the doctor. All participants will be required to have a mobile phone, and will be issued a power-bank to keep their phone charged during power-outages. Participants will be issued an antibiotic course at the point of experimental inoculation and will be instructed to keep them on their person, and on when/if to take them. The pneumococcal isolate used during experimental inoculation is microbiologically and genetically confirmed antibiotic-susceptible. Participants will have the relevant safety information written in English and Chichewa on laminated, pocket-sized cards.

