### Sample size calculation

The study will recruit 75 PLHIV and 75 HIV-negative controls aged 25–45 years old. The sample size is based on 50% carriage rate following inoculation in HIV-negative controls
^
17
^, and a 50% greater carriage rate amongst PLHIV based on community carriage point-prevalence
^
21
^. 132 participants (66 per group) will be required to achieve 80% power with p=0.05 so 150 participants will allow for some participant drop-out.

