### Statistical analysis

Descriptive statistics will be used to describe group characteristics and to describes rate of pneumococcal carriage in both groups. Pneumococcal carriage rate will be described by area-under the curve of carriage density over the duration of follow up, and as a binary carriage positive (at any time) compared to carriage negative. Natural carriage and baseline serum concentrations of commonly used antibiotics (e.g. cotrimoxazole) will be included as a variable in the regression. Two-tailed comparisons will be performed to evaluate density and activation of immune cell populations, and immunoglobulin concentrations between those who become colonised with pneumococcus and those who do not in PLHIV and HIV-negative controls. Paired comparisons will be performed to compare density and activation of immune cell populations before and after pneumococcal inoculation. Multiple comparisons will be adjusted for using Benjamini-Hochberg or Bonferroni methods
^
22
^.

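### As worded, the colonised versus non-colonised immune comparisons leave out the baseline antibiotic level, so in PLHIV a marker that tracks prophylaxis use could pass for a correlate of protection

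*Protocol article*

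**What the plan says.** Objective 3 is stated as: "Identify the immune correlates of protection from pneumococcal carriage in PLHIV following experimental pneumococcal inoculation". The Statistical analysis section serves it with two-group tests: "Two-tailed comparisons will be performed to evaluate density and activation of immune cell populations, and immunoglobulin concentrations between those who become colonised", against those who do not, in PLHIV and in controls. Paired before-and-after comparisons follow. The only adjustment named for these tests is for multiplicity.

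Antibiotic exposure appears one sentence earlier, straight after the description of carriage rate: "Natural carriage and baseline serum concentrations of commonly used antibiotics (e.g. cotrimoxazole) will be included as a variable in the regression". The outcome of that regression is not named.

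Four other places bear on the point:
- **Exclusion criteria.** A recent antibiotic course excludes a participant, but prophylaxis in PLHIV is exempt.
- **Sampling methods.** Blood is drawn among other things "to evaluate peri-inoculation serum levels of commonly used antibiotics".
- **Safety monitoring.** "The pneumococcal isolate used during experimental inoculation is microbiologically and genetically confirmed antibiotic-susceptible".
- **Determination of colonisation.** "Pneumococcal colonisation is defined as the detection of pneumococcus serotype 6B by microbiological culture in nasal wash samples at any of the time points". Sampling runs from day 2 to day 21. Everyone else is non-colonised, whatever the reason.

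**The concern.** The protocol treats antibiotic level as relevant to carriage, measures it, and uses it in one model. The analysis that divides participants by carriage is then described without it. If a prophylactic drug prevents 6B carriage in some PLHIV, the non-colonised group contains proportionally more drug users than the colonised group. Two effects follow:

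- **Confounding.** A marker with no protective role that happens to differ between users and non-users will also differ between non-colonised and colonised PLHIV.
- **Dilution.** A truly protective marker shows a smaller difference, because some susceptible people sit in the non-colonised group.

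The exemption applies only to PLHIV, so both effects are expected mainly there. The Discussion intends the correlates to guide vaccine immunogenicity evaluation, so a false or missed correlate has consequences beyond this study.

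**Working it through.** **1. The plan's own figure.** The Sample size calculation says: "The sample size is based on 50% carriage rate following inoculation in HIV-negative controls". It assumes a rate 50% greater in PLHIV, read here as relative, so 75%. For two proportions, two-sided 5%, 80% power:

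n = [1.96 × √(2 × 0.625 × 0.375) + 0.842 × √(0.25 + 0.1875)]² / 0.25² = 57.7, so 58 per group.

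With the continuity correction this becomes 66 per group, as stated. The point does not turn on a wrong sample size. The 66 PLHIV and 75% carriage are used below.

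**2. Assumed inputs.** The documents do not give the share of PLHIV on prophylaxis (f), the drug's effect on 6B carriage, or any link between drug use and a marker. Take f = 0.5, with carriage off/on drug of 85%/65% (A) or 90%/60% (B). Both average 75%.

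**3. Make-up of the non-colonised group.** Non-carriers number 66 × 0.25 = 16.5.

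| | A | B |
|---|---|---|
| Non-carriers explained by drug: f × (off − on) / 0.25 | 0.5 × 0.20 / 0.25 = 40% | 0.5 × 0.30 / 0.25 = 60% |
| Users among non-carriers: f × (1 − on) / 0.25 | 0.5 × 0.35 / 0.25 = 70% | 0.5 × 0.40 / 0.25 = 80% |
| Users among carriers: f × on / 0.75 | 0.5 × 0.65 / 0.75 = 43% | 0.5 × 0.60 / 0.75 = 40% |

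**4. A marker with no protective role.** If it differs by δ SD between users and non-users, the expected spurious difference between colonisation groups is δ times the difference in user share:
- A: 0.27 × δ, so 0.13 to 0.27 SD for δ = 0.5 to 1.
- B: 0.40 × δ, so 0.20 to 0.40 SD.

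The standard error of a two-group difference, per SD, is about √(1/16.5 + 1/49.5) = 0.28. The shift is therefore roughly 0.5 to 1.4 standard errors. Simulated rejection rates at nominal 5% (1,500 trials per setting):

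| | δ = 0.5 | δ = 1 |
|---|---|---|
| A, unadjusted | 6.8% | 12.8% |
| B, unadjusted | 11.4% | 23.7% |
| With antibiotic term | 4.3 to 6.5% across settings | |

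Monte Carlo error is at most about √(0.237 × 0.763 / 1500) = 1.1 points.

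**5. A marker that is protective.** In A, a true standardised difference of 0.96 is seen as 0.56. Adjustment hardly repairs this. Measured in SDs of the marker over all PLHIV, the difference moves from 0.53 unadjusted to 0.56 adjusted, and power rises by about 1 to 4 points (for example 46% to 50%).

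**6. A different anchor.** Now let 75% be the drug-free rate, with 75 PLHIV, 25 to 50% exposed and a drug effect of 50 to 90%:
- The drug-explained share of non-carriers is 27 to 57%.
- False positives at δ = 0.5 are 8 to 29% unadjusted and 4 to 6% adjusted.
- A 0.71 SD difference falls to 0.30 to 0.53, and adjustment brings it to 0.47 to 0.66, with 5 to 21 points more power.

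These settings imply overall PLHIV carriage of 41 to 66%, below the planned 75%. The confounding result is the same under both anchors. How much of the dilution is recovered depends on the anchor, and it is never all of it.

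**7. Antibiotic-negative subset.** Non-carriers there number 33 × 0.15 = about 5 in A and 33 × 0.10 = about 3 in B.

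**The case against.** The strongest reply is that this is a condensed article. The regression's outcome is unnamed and could include the immune markers. Calling tests two-tailed fixes their sidedness and does not rule out covariates, and covariate lists are often left to an analysis plan. Part of that stands: the authors may intend the adjustment. But the text names the covariate, ties it to one analysis, and words the immune analysis as a different one with only a multiplicity correction. One sentence would settle it.

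Several limits also stand:
- Susceptibility to cotrimoxazole, the one drug named as an example, is never stated.
- No passage shows a marker that differs between users and non-users. Without such a link there is dilution but no false correlate.
- The Primary outcomes section labels the immune-cell work exploratory, though not the immunoglobulin outcomes.
- The rates above are per test at nominal 5%, before Benjamini-Hochberg or Bonferroni. Those methods limit chance findings but do not remove a systematic difference.
- With about 16 non-carriers, any model must be small.

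A reader might also infer that the plan counts every non-colonised PLHIV as protected by immunity. The documents do not say so. Measuring and modelling antibiotic levels suggests the authors know of another reason for non-carriage.

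**Conclusion.** The point holds as a specific weakness in how the objective 3 comparisons are worded. Under the stated assumptions, leaving out the antibiotic result raises the per-test false-positive rate in PLHIV from 5% to about 7 to 24%, and including it restores about 5%. All of this rests on assumed exposure, drug effect and marker differences, because the documents supply none of them.

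Three stronger readings are not supported:
- **That users and non-users certainly coexist among PLHIV.** No prophylaxis rate is given. If nearly all or very few PLHIV take prophylaxis, adjustment gains little.
- **That adjustment restores diluted correlates.** At the planned 75% carriage it adds about 1 to 4 points of power.
- **That the plan would read a correlate present in controls but absent in PLHIV as an immune defect.** The second hypothesis says "PLHIV will have perturbed mucosal and systemic immunity in response to experimental pneumococcal inoculation" relative to controls, but sets no such rule. Because dilution remains after adjustment, that pattern should not by itself be taken as a defect.

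**What to change.** In the Statistical analysis section:

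1. Name the outcome of the regression that contains natural carriage and antibiotic level.
2. State that colonised versus non-colonised comparisons of pre-inoculation immune measures within PLHIV adjust for the baseline antibiotic result. Examples are a linear model of the marker on colonisation and antibiotic detected (yes/no), or a penalised logistic model of colonisation on the marker and antibiotic detected.
3. Report the share of PLHIV with antibiotic detected, so that readers can judge how much the adjustment could matter.
4. State that a correlate seen in controls and absent in PLHIV is not, on its own, evidence of an immune defect.

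A repeat in PLHIV with no antibiotic detected is optional and should be descriptive, since it may hold only about 5 non-carriers.

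The cost is one degree of freedom and one already collected covariate. No sampling, eligibility or clinical management changes.

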### Adverse event and serious adverse event monitoring

Reported and solicited adverse events (AEs) will be collected systematically during the research and recorded in the case report form. Any serious adverse event (SAE) occurring to a research participant will be reported within 24 hours to an independent Data, Safety and Monitoring Board (DSMB), to the ethical review board, and to the study sponsor. The DSMB consists of three professors of infectious diseases, and one professor of statistics based in Malawi and internationally. In the event of an SAE (death, hospitalisation, life-threatening, and significant disability), the research will be stopped temporarily for investigation and any further work deferred until advice has been provided.

## Ethical approval

The study protocol has been approved by the National Health Sciences Research Committee of Malawi (22/09/3053), and by the Liverpool School of Tropical Medicine Research Ethics Committee (22-077).

## Study registration

Clinicaltrials.gov registry number NCT05698225.

## Remuneration

Participants will be compensated for time, transport, subsistence, and discomfort experienced. Remuneration amounts have been calculated using local Malawi College of Medicine Research Ethics Committee guidelines
^
23
^. Participants will not be remunerated for the information visit. Remuneration will be given in cash at each study visit (18 500 Malawian Kwacha per visit, 130 000 Malawian Kwacha if all study-visits are completed).

## Confidentially and anonymity

Only authorised members of the research team will have access to any personal information. Only information of direct relevance to the study will be collected. All electronic records containing personal information will be stored in a password protected database on a password protected server at MLW. Electronic case report form data will be collected on encrypted study-specific tablet devices and synchronised daily onto the MLW server. Each researcher will only be able to view the information required to fulfil their role in the study. This approach is well established at MLW, and the policy governing MLW data management policy is available upon request. Paper documentation containing personal information will be kept in a locked filing cabinet in a locked room in the Queen Elizabeth Central Hospital research clinic. Each participant will be assigned a unique non-identifiable study number by a member of the clinical research team at recruitment. Unlinked non-identifiable clinical data will be stored and analysed at the MLW-laboratories and collaborating laboratories.

## Samples and data

MLW will act as custodian for all data and samples collected during the study. Consent will be obtained from the participant to use the samples for this research only. Samples will be stored for a maximum of five years. Laboratory samples will also be sent to national and international collaborating laboratories to utilise specialist expertise not available in Malawi. Samples will be labelled with the anonymised study number. Consent will specifically be obtained from the participants to allow samples to be sent to our collaborators.

## Dissemination of findings

The findings from this study will be disseminated amongst the scientific community. We intend to publish our findings in peer-reviewed scientific journals and present data at appropriate local, national and international conferences. We will produce a close-out report for the ethical review committees at the end of the study and a final report once data are published. In addition, we will produce a lay report of our findings which will be made available to all participants.

## Discussion

PLHIV remain a key population to consider when addressing the burden of pneumococcal disease, particularly in settings with high HIV prevalence. They are at risk of disease themselves and are at risk of driving onward transmission of the bacteria in vaccinated communities. An evidence-base to guide vaccination policy is lacking. A trial of Ugandan adults with PLHIV demonstrated increased rates of pneumococcal disease associated with PPV23 vaccination
^
12,
13
^. A trial of Malawian adults with PLHIV demonstrated safety and efficacy against vaccine-serotype disease with PCV7 administation
^
14
^. However, PCV7 has limited serotype coverage and gives rise to ‘serotype replacement’ in which an increase in non-vaccine serotype disease limits overall vaccine effectiveness against pneumococcal disease
^
15
^. The British HIV Association and European AIDS Clinical Society recommend the routine use of PCV13 in PLHIV but do not recommend against giving PPV23 if administration meets other national recommendations (e.g. vaccinating over 65 year olds)
^
24,
25
^. The National Institute of Health recommends PCV15 with PPV23 at least 8 weeks later, or PCV20
^
26
^. Guidelines for a sub-Saharan African settings are absent. This study will transform the evidence-base for pneumococcal vaccination in PLHIV in sub-Saharan Africa by establishing a model for efficient vaccine-efficacy trials, and by identifying the immune correlates of protection from pneumococcal carriage to guide more effective vaccine immunogenicity evaluations.

This will be the first CHIM study in PLHIV and participant safety is paramount. Natural pneumococcal carriage does not often result in invasive disease, and is a ubiquitous event in the study population. The point prevalence of natural pneumococcal carriage in PLHIV in Malawi ranges between 26% and 52%, depending on urban or rural settings
^
5,
6,
9,
27
^. In a six to ten month period, 99% of PLHIV will experience at least one pneumococcal carriage event, and on average adults will experience five separate pneumococcal carriage events
^
28
^. Meanwhile, the rate of pneumococcal disease in sub-Saharan Africa in the post-ART era is estimated at 318 per 100 000 population
^
29
^. Pneumococcal carriage increases with the initiation of ART, compared to the ART-naïve, meaning as ART is rolled-out across sub-Saharan Africa, pneumococcal carriage rates are increasing
^
5,
6
^. Meanwhile, pneumococcal disease rate is reduced by a half to a third by ART, and rates of HIV-associated hospital admissions in Malawi have halved as ART is rolled out in the country
^
30,
31
^. Thus it can be inferred that the ratio of natural pneumococcal carriage to pneumococcal disease is very small and improves on ART. Experimental carriage is expected to be a similar benign event. Safety in this study is further enhanced by careful participant selection and by pneumococcal serotype selection. The exclusion criteria ensure that participants are well and stable on antiretroviral therapy. Risk of developing pneumococcal disease is strongly associated with CD4 T cell count
^
32
^, and all participants in this study will be immune-reconstituted and without additional risk factors for invasive pneumococcal disease. The pneumococcal serotype 6B used in the study has been selected for a lower carriage to disease ratio than other serotypes
^
33
^. Less than 2% of invasive pneumococcal isolates in Malawi are caused by serotype 6B and are largely seen in children if at all
^
34,
35
^.

Public and participant perception are a key consideration for CHIM studies in sub-Saharan Africa. The acceptability of the EHPC model to Malawian medical, research, and community stakeholders has been evaluated and provides a framework for this study to address ethical and safety considerations
^
18
^. For example, the study will use passive recruitment tactics to avoid potential participants feeling pressured by direct solicitation, as identified by stakeholder consultation. Reasons for participation in EHPC studies have been explored in detail in Malawi and provides guidance for avoiding undue solicitation during recruitment
^
36
^. Conducting a CHIM in PLHIV has been positively perceived by HIV stakeholders in Malawi during preliminary evaluations. The importance of giving PLHIV the opportunity to participate in research for the sake of equity and autonomy has been highlighted, while the need to balance risk to participants is recognised. Acceptability will be explored in a stand-alone study using qualitative methods running concurrently with this study.

## Conclusion

This first CHIM in PLHIV can be conducted safely and is acceptable to local stakeholders. The findings from this study will explain high pneumococcal carriage rates observed in PLHIV and will identify potential strategies to address the issue. The study will facilitate effective and efficient pneumococcal vaccine evaluations in PLHIV, and thus guide policy makers in addressing the burden of pneumococcal carriage in PLHIV in sub-Sharan Africa.

